#### Power calculations

3.4.3

Based on data published previously (behavioural intervention K10 change 21.2 ± 9.4 vs baseline 25.7 ± 9.7 Cohen d = 0.5), a sample size of 64 per group in the primary RCT will be required to identify a moderate effect size of 0.5 between intervention and control group, in a *t*-test model with power = 0.8, alpha 0.05. An additional 14 participants will be included to allow for an attrition rate of 10 % (total n = 142). The nested exploratory RCT (No MHC) is considered an exploratory study as it could not be powered.

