##### Intervention

3.3.2.6

The intervention delivered to the MHC and No MHC studies will be identical. All participants will receive standard diabetes care through their regular clinic. This includes education sessions, a food diary, self-management practices such as blood glucose monitoring, healthy eating, regular clinic attendance with review of blood glucose monitoring and weight measurements conducted either by the educator and/or endocrinologist. Participants will receive a physical activity tracker and have access to Peer Support facilitated by people with lived experience of diabetes. Availability of Peer Support is considered part of best practice standard care [24] and will be available at the outpatient clinics of the study sites included in this trial. It is already available at some sites and will be established at sites without existing Peer Support during the trial set-up phase. Peer support can be provided digitally (e.g., ad hoc Facebook communication, Zoom meetings) or through one-on-one or group face-to-face meetings, with the topic focus, frequency and duration determined by the peers or peer support facilitators.

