### Statistical analysis

3.4

For the primary outcome variable (K10), a linear mixed effects regression model will be used to show any change, with participant identification number and study site as random effects. Age, gender, ethnicity, socio-economic status, type of diabetes, time and intervention group will be included as fixed effects. A significant interaction between intervention group and time (Baseline vs Follow Up) would indicate that the average change in K10 was significantly different between intervention and control groups [31]. This is the main test of the study and will be subjected to a significance level of α = 0.05. Level of significance will also be indicated using p-values. The effect sizes will be presented as the difference between the average decrease in K10 between intervention groups.

A linear mixed effects regression model will also be used for the secondary outcome variables including a change in; (1) HbA1c (2) PAID and (3) weight in kilograms. To account for multiple testing, a false discovery rate method such as the Benjamini-Hochberg procedure [32], will be adopted for the secondary outcome variables. The effect sizes will be presented as the difference between the average change in outcome between intervention groups. Results will be visualised using a forest plots. For all linear mixed effects models, model diagnostics will be conducted, including, but not limited to (a) examining the residuals for departures from normality, (b) collinearity between covariates using the variation inflation factor and (c) examination of outliers to see if they have too much influence on the results of the analysis. Consequential departures from normality and/or highly influential outliers will be handled using bootstrapping or through transformation of the outcome variable.

A generalised linear mixed effects regression model with a Poisson error model [33] will also be used for the secondary outcome variables; (4) the total number of hospital and/or emergency department admissions and (5) the total number of hospital and/or emergency department admissions due to diabetic keto-acidosis/hyperglycaemia. The models will be examined for over or under dispersion and a more appropriate error model will be adopted if necessary.

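### The between-arm K10 effect of 0.5 is justified by a before-after change whose own standardised size is 0.47; for that change 64 per arm gives about 75% power, not 80%

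*Protocol article*

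**What the plan says.** Section 3.4.3 bases the effect size on earlier published data, given as "behavioural intervention K10 change 21.2 ± 9.4 vs baseline 25.7 ± 9.7 Cohen d = 0.5". The next step sizes the primary RCT for a contrast with the control group: "a sample size of 64 per group in the primary RCT will be required to identify a moderate effect size of 0.5 between intervention". The model is a t-test with "power = 0.8, alpha 0.05". This gives 64 per group, and 14 more participants for 10% attrition bring the total to 142.

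Section 3.4 (Statistical analysis) makes the interaction of group and time on K10 the primary test: "This is the main test of the study and will be subjected to a significance level of α = 0.05". The effect is to be reported as the difference between arms in mean K10 decrease.

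Two other sections bear on what controls may do. Section 3.3.2.6 (Intervention) applies to both arms: "Participants will receive a physical activity tracker and have access to Peer Support facilitated by people with lived experience of diabetes". Section 3.3.2.4 makes a K10 score of 20 or more one of several routes into the primary RCT. The Discussion (section 7) repeats the 0.5 target without giving another basis for it.

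**The concern.** Two things do not fit.

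First, the quoted figures compare a treated group with its own baseline, while the quantity powered is a contrast between app and control. The two are equal only if the control arm has zero mean change. The design gives reasons to doubt that: controls also receive a tracker and access to peer support, and some participants enter because their K10 was high at screening, so some fall towards the mean is possible in both arms.

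Second, the quoted means and SDs do not give 0.5. They give a slightly smaller value, and sample size is sensitive to that because it varies with the inverse square of the effect.

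At stake is how the result is read. The section presents 80% power as resting on published data. For the change in those data, the trial as sized has less than that, and a null result could be given more weight against such an effect than it can bear.

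**Working it through.** **Inputs**, all from section 3.4.3: baseline K10 25.7 (SD 9.7); K10 after intervention 21.2 (SD 9.4); stated d = 0.5; two-sample t-test; alpha 0.05; power 0.80; 64 per group; 10% attrition. Two readings are needed. The 21.2 is taken as the follow-up score, since it is set against baseline. Alpha is taken as two-sided, because that reproduces the stated size (a one-sided test needs about 50 per arm).

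**1. The plan's own figure.** By the normal approximation, n per arm = 2(1.96 + 0.84)²/d² = 15.7/0.25, about 63. The exact noncentral-t solution is 63.8, so 64 per arm, with power 80.1%. Attrition: 2 × 64 = 128; 128/0.9 = 142.2, against 142 stated. Both figures reproduce.

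**2. Effect size from the quoted data.**
- Difference: 25.7 − 21.2 = 4.5 points.
- Pooled SD: √((9.4² + 9.7²)/2) = √((88.36 + 94.09)/2) = √91.225 = 9.55.
- d = 4.5/9.55 = 0.471.
- With the baseline SD alone: 4.5/9.7 = 0.464. With the follow-up SD alone: 4.5/9.4 = 0.479. Neither gives 0.50.

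**3. Power for the cited change, assuming no change in controls.** The noncentrality is d√(n/2) = 0.471 × √32 = 2.67, on 126 degrees of freedom. Power is 75.3% (74.0% at d = 0.464, 76.7% at d = 0.479). For 80% at d = 0.471 the exact solution is 71.7, so 72 per arm; that is 144 evaluable and 144/0.9 = 160 recruited, against 142.

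**4. What 64 per arm does deliver.** 0.5 × 9.55 = 4.78, so 80% power applies to a net difference of about 4.8 K10 points.

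**5. Illustration of control change.** The control falls here are assumptions; the documents give none. The app arm's total fall is held at 4.5 points.

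| Assumed control fall | Net difference | d | Power at 64 per arm |
|---|---|---|---|
| 0 | 4.5 | 0.471 | 75% |
| 1 | 3.5 | 0.366 | 54% |
| 2 | 2.5 | 0.262 | 31% |

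**The case against.** The strongest reply is that the protocol claims 80% power for a standardised effect of 0.5, not for 4.5 K10 points, and that this claim is correct. Rounding 0.471 to 0.5 is right to one decimal. If 0.5 had been chosen as a target difference in its own right, 64 per group would be adequate. The arithmetic part of this stands. But the section offers the before-after data as the basis for 0.5, and no other basis appears in the article.

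A second reply concerns control change. Trackers, peer support and K10-based entry apply to both arms, and randomisation balances regression to the mean. Shared improvement shrinks the net difference only if the app arm's total change stays near 4.5 points. That also stands. A reader might infer from the table that power is well below 80%; the documents do not support this, because no figure in them fixes the control change. Nor do they show whether the cited study had a control arm. They show only that the figures quoted from it are before versus after.

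A third reply is that the planned test compares changes, so its power depends on the correlation between baseline and six months. For 4.5 points with no control change, power would be 61% at a correlation of 0.3, 75% at 0.5, 80% at about 0.56 and 93% at 0.7. A reader might infer that the t-test calculation misstates power in a known direction. It does not: the effect could go either way, and an article may leave the assumed correlation to the full protocol or SAP. It is no part of this point.

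**Conclusion.** The concern holds for the effect-size input. A pre-post change of 4.5 points, with d = 0.47, is used as a between-arm effect of 0.5. In the stated t-test model, 64 per arm gives about 75% power for the cited change if controls do not change. That is about 5 percentage points short, and 72 per arm would be needed for 80%. This result rests only on the quoted means and SDs, a two-sided alpha of 0.05 and zero control change. Anything lower depends on a control improvement that has to be assumed.

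It does not follow that 142 is miscalculated or that the trial must be enlarged. Severity is moderate: the stated justification needs correcting, while the test, the estimand and the sample size can stay as they are.

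**What to change.** Keep n = 142 and restate section 3.4.3 along these lines:

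- With 64 evaluable participants per arm, a two-sided t-test at alpha 0.05 has 80% power for a net app-versus-control difference of about 4.8 K10 points (0.5 SD, with SD 9.55).
- The published change of 4.5 points is a before-after figure with no control change subtracted. Its standardised size is 0.47, and power for a net difference of that size is about 75%.
- Any improvement in controls that is subtracted from 4.5 points lowers power; under assumed control falls of 1 or 2 points it would be 54% or 31%. Label these as illustration.

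If the trial team has an independent reason to treat about 4.8 points as the difference worth detecting, it should be given here in place of the before-after data.

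The cost is some rewording and a less favourable power statement. No participants are added, and neither the analysis nor any trial procedure changes.

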#### Data management

3.4.4

A customised web-based data capture system (BTR; Western Sydney University, Australia) will be employed to gather data, which will be stored at the primary analysis and study coordination site located at Western Sydney University, Campbelltown, Australia. Perx will capture app metrics, including enrolment details, app utilisation (e.g., average sessions per day, average time spent in the app per month, utilisation of diabetes and mental health resources), task and medication adherence, participant satisfaction, and content engagement. The time spent using the app, linked to in-app communications is considered an exploratory outcome.

## The role of Perx Health in APHLID-M

5

The app provider, Perx, are contractors and will receive payment through the grant. Perx will not fund any part of the study or have input into the study design. Perx's role is limited to supplying the platform and managing the configuration of the existing Perx app to include diabetes and mental health resources, identified and agreed upon by the app configuration group. Additionally, Perx will oversee the onboarding of participants assigned to the app group but will not be involved in data analysis or interpretation of study results.

## Dissemination of findings

6

Results will be disseminated in peer-reviewed publications, at scientific meetings, through collaborations and discussions with stakeholders and policy makers.

## Discussion

7

This is the first multi-site RCT to evaluate whether a configured health “app” containing diabetes and mental health app improves psychological distress, well-being, and physical health in young adults with diabetes and a MHC. The design allows for a parallel exploratory RCT among those without a MHC.

In this study the K10 will be used as a tool to screen for psychological distress (primary outcome measure), as it offers a broad, general assessment of mental health [21]. This decision was based on the high levels of psychological distress and other mental health challenges commonly experienced by young people with diabetes [37,38]. Additionally, when diabetes co-occurs with mental health disorders, there is a cumulative effect on both mental and physical health, leading to a reduced quality of life [39,40]. The K10, widely used internationally, enables comparison of distress levels across diverse clinical conditions (Kessler et al., 2003) providing a more comprehensive measure of MHC beyond diabetes. In contrast, the PAID scale specifically measures diabetes-related distress [22], which, while valuable, limits the scope of the distress captured to diabetes-related stressors only. Since the APHLID-M study aims to address mental health needs of young people with diabetes, HbA1c was designated as a secondary outcome, with its relationship to psychological distress to be explored in the analysis.

The APHLID-M study design integrates peer support and the use of activity trackers for all participants. Peer support, is a standard part of care across all study sites and has been shown to be beneficial for managing mental health conditions in people with diabetes [41] and improve behavioural outcomes (e.g., medication adherence), psychosocial factors (e.g., diabetes distress), and health measures (e.g., blood glucose levels and HbA1c) in people with diabetes [42]. Activity trackers are provided to participants to incentivise participation, promote engagement and adherence to physical activity and health goals throughout the study. This approach addresses both psychological and physical aspects of diabetes, contributing to better overall well-being and clinical outcomes.

While it is anticipated that most participants recruited from the hospital clinics will have T1DM, people with T2DM or rare forms of diabetes will also be included in this study, and as such the app was correspondingly configured to contain two Health Hubs. The inclusion of people with T2DM is important as they also experience significant mental health challenges [43] and are at elevated risk for long-term diabetes related complications [44]. This approach will enable the evaluation of the intervention's effectiveness across different diabetes phenotypes and aligns with the study's objectives to improve both diabetes and mental health outcomes. It also ensures the intervention's applicability across different diabetes types. Additionally, recruiting all young adults and then allocating them to study groups based on mental health status helps reduce the stigma often associated with mental health in diabetes [45].

A key strength of this study is its RCT design, with blinding of the research team, which ensures a high level of scientific rigor by minimising bias and allowing for a clear evaluation of the apps impact on mental health and diabetes outcomes. Another key strength of the study design is the inclusion of participants aged 16–30 years, capturing young patients across a wide age range enabling a comprehensive analysis of how the app intervention impacts mental health and diabetes outcomes across the 16 to 30-year age range. Including participants from both urban and rural areas enhances the study's generalisability, ensuring its findings are applicable across different geographic and socio-economic settings. The inclusion of a health economic analysis and qualitative evaluation of participants experience using the app further enhances the value of this study.

The sample size of the primary RCT (n = 142) was calculated allowing for a 10 % loss to follow-up. However greater loss to follow-up due to poor participant attendance at follow-up assessments could impact the ability to detect a moderate effect size of 0.5 in K10 score between intervention and control group. Given that the participants are attending clinical services and the trial duration short, it is hoped that follow-up targets are achieved. Nonetheless participant responsiveness is uncertain. To minimise loss to follow-up, participants will be contacted via text messages, email, and clinic or study phones as necessary. Additionally, the short follow-up period limits insights into the sustainability of the effects if observed. Due to the smaller sample size expected in the nested exploratory No-MHC arm, no independent power calculations were performed. Despite separate registrations, both groups will receive identical interventions and follow the same study procedures. Publishing a single protocol paper ensures clarity, avoids unnecessary duplication, and maintains consistency in reporting across both study arms. While a formal pilot study specific to youth with diabetes has not been conducted, the platform has been used among young people with cystic fibrosis, some of whom have cystic fibrosis related diabetes. Nevertheless, a post-trial qualitative analysis will be undertaken with participants randomised to the app, to assess user experience and gather suggestions for improvements.

In conclusion, the APHLID-M study represents the first multi-site RCT to assess the effectiveness of an app containing diabetes and mental health resources in improving mental health, well-being, and physical health in young adults with diabetes with and without MHC. The study incorporates peer support and activity trackers to promote participant engagement and behaviour change and improve health outcomes. Data from activity trackers will be collected where available. With its diverse cohort of paediatric and adult participants from both urban and rural settings, the study aims to provide valuable insights into how the intervention can be scaled and its potential impact on reducing healthcare costs. While challenges related to follow-up rates and sustainability exist, the study's design ensures robust evaluation of the intervention's effect on mental health and diabetes outcomes across different populations and settings.

## Ethics approval

4

The study was approved by the South Western Sydney Local Health District Human Research Ethics Committee (reference PID:2022/02828, 2022/ETH02515).

## Ethics approval

Ethics approval: South Western Sydney Local Health District Human Research and Ethics Office (reference PID:2022/02828, 2022/ETH02515).

## Trial registration

Australian New Zealand Clinical Trials Registry, ACTRN12623000734662 (Primary RCT; mental health condition) and ACTRN12623000733673 (nested exploratory RCT; No mental health condition)

